### Outcomes

Using questionnaires, interviews, exercise-tests, a 6-minute walk test (6-MWT), interrogation of the ICD and register-based follow-up, the effect and meaning of the programme are evaluated (Table 2). The pre-training exercise test is performed at 3 months and therefore not reported here.

**Table 2 T2:** Outcome Measures

Measurement	Time
**SF-36**	Baseline, 3-6-12 month

QLI-C	Baseline, 3-6-12 month

IDAS	Baseline, 3-6-12 month

Sex after ICD survey	6 month

ICD and Avoidance Survey	6-12 month

SCA knowledge assessment	Baseline, 12 month

**Exercise test**, 6MWT	3-6 month

ICD interrogation	3-6-12 month

Work	12 month

Rehabilitation elsewhere	12 month

Qualitative interview	12 month

Registry data	2 years

SF-36 and exercise test are primary outcome measures.

Primary outcome measures: Due to the nature of rehabilitation, including both physical and psychological components, the two primary outcome measures are perceived health measured by the Short Form-36 [33,34] questionnaire and Peak VO2, measured by a standardized protocol according to guidelines [35]. The test is performed on bicycle ergometer with an initial workload of 12.5 W and increased 12.5 w every minute until exhaustion or at 5 beats/min heart rate below ICD activation threshold. No gas analyses are conducted.

Secondary outcome measures: Physical capability is measured by an exercise test combined with the six minutes walk tests which have been proved to be effective measures of functional capacity in patients performing cardiac rehabilitation [30,36,37]. Further, exercise training data consist of the number of sessions, duration and heart rate.

Ventricular arrhythmia: 1. ICD-shock 2. Anti-tachycardia pacing is registered by interrogation of the ICD.

Questionnaires: Quality of life is measured by Quality of Life Index-Cardiac version (QLI-C) [38], knowledge of the ICD by Sudden Cardiac Death (SCD) knowledge assessment [20], ICD-adaptation using Implanted Devices Adjustment Scale (IDAS) [39], sexual problems or dysfunction by the Sex After ICD Survey [40] and avoidance behaviour is measured by ICD and Avoidance Survey [40].

Ancillary questions developed for this study: amount of participation in rehabilitation outside the project, and work status/sick leave before and after ICD implantation.

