### Sample size

#### Physical capacity

Based on current knowledge (1), we estimate a difference in V02max of 15% between the rehabilitation group and standard care group (SD = 0.3). A total number of 128 patients are estimated for the trial (alfa = 5%, beta = 20%). *Health status outcome measure: *Based on health status measures among a Danish population compared to patient with heart disease a baseline mean-score of the SF-36 general health (GH) is estimated to be 60 (SD = 22). The effect of rehabilitation is expected to be 10 absolute points. A total number of 154 patients are needed in the trial (alfa = 5%, beta = 20%). The study includes 196 patients, taking a drop-out rate of 20% into account. In the previous trials a drop-out rate around 20% was found, with no significant differences in baseline information on any study variable between groups and no difference in the number of dropouts in each group [11,17,19,21,23].

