### Statistical methods

The statistical analyses of the effects of rehabilitation are conducted based on a predefined statistical protocol using SPSS 17.0 for Windows. The analysis will adopt an analytical approach on all available data, meaning that all data obtained are included in analyses, regardless of adherence to the study protocol. Only data from patients following through the program will be included in the analysis of the endpoints. Accordingly, there is no imputation of missing data. Questionnaire responses will be converted to numerical scores using standard methodologies. Continuous data are checked for normality of distribution, and log-transformed if required. The baseline characteristics will be presented by group to present similarities across treatment, but according to recommendations no significant testing will be performed [43]. The socio-demographic and clinical characteristics of individuals who drop out from the study will be compared with those who completed the study and drop-out characteristics between groups will be compared. The effectiveness of the intervention will be examined using blinded analysis of variance. The primary comparisons will be Two independent samples T-test for the mean difference between two independent samples. Paired T-tests of equality of means will be used for within group analysis of difference over time. Further, univariable and multivariable regression analysis will also be used to investigate the effect of the intervention on the endpoints. The type of regression analysis will depend on the endpoint in question. Demographic, clinical and questionnaire data will be included in multivariable analysis in order to control for their potential confounding effects. The level of significance is set at p < 0.05. Data will, for continues data, be shown as means ± standard deviation or percentage. Categorical data will be shown as percent. Twelve month follow-up data and results obtained from Danish registries regarding hospitalisations are used for follow-up comparison. Due to the skewed distribution of length of hospital stay and repeated measurements of hospital admissions on patients these register-based tertiary outcomes will be analyzed using multivariate random-effect modelling with patients as random effects. Further analysis will be conducted using the Cox regression model including time to first event as outcome variable. At baseline 46% (n = 91) of the population was employed. This is a rather small number of patients and sickness absence will be included as a measure when evaluating employment status. The direct costs of healthcare are calculated by a retrospective top-down method [44]. All other costs are extracted from relevant registers.

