## Discussion

Demographic data and clinical variables are similar between the groups. The baseline characteristics are similar to other ICD rehabilitation populations regarding NYHA, LVEF, gender, type of device and indication [20,21]. The baseline measures of knowledge and skills needed to live with an ICD, SCA Knowledge score 20, are similar to the ICD rehabilitation population that originally tested the questionnaire, score 21 [20]. The population is also similar to other ICD populations regarding quality of life, with very similar scores in all subscales [47,48]. Perceived health measured by SF-36 is also similar to other findings as to the mental and emotional health, but with somewhat higher scores in physical function and pain [48].

Testing 6-MWT showed that this population might have a higher physical capacity (417 m) than other ICD populations (328 m, 383 m) [49,50], which can possibly be explained by a slightly higher LVEF and younger age.

This intervention is expensive from a rehabilitation perspective with 9 nurse consultations, 2 individual consultations with a physiotherapist and 2 weekly exercise training group sessions offered at the hospital. The planned economic analysis will reveal the cost-benefit ratio of this comprehensive rehabilitations programme. The set-up of this programme can be done in any cardiac rehabilitation setting after proper education of nurses and physiotherapists.

Study limitations include the fact that that selection bias may exist due to patients not being included if they were already included in a pharmaceutical trial. The control group might be contaminated by the information given during the project inclusion, suggesting that psycho-educational assistance and exercise training might be beneficial after ICD implantation. This information could lead to control patients seeking rehabilitation elsewhere if they believe it is effective. There is an expected drop-out rate at 20% which could influence the validity. Any difference between patients completing the intervention and those not completing (drop-outs) will be carefully discussed in evaluating the intervention, results and the suitability for implementation. The trial is designed with multiple statistical comparisons so results will be interpreted with caution.

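### Two unordered primary outcomes are each tested at 5% with no rule for combining them; if either counts as success, the error rate is about 9 to 10%, not 5%

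*Protocol article*

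**What the plan says.** The Outcomes section explains that rehabilitation has physical and psychological parts, and therefore "the two primary outcome measures are perceived health measured by the Short Form-36" questionnaire and peak VO2 on a bicycle test. The note under Table 2 repeats this without ranking them: "SF-36 and exercise test are primary outcome measures".

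The Sample size section treats the two outcomes separately, each with 5% alpha and 20% beta:

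- Exercise capacity: "we estimate a difference in V02max of 15% between the rehabilitation group and standard care group (SD = 0.3"), leading to "A total number of 128 patients are estimated for the trial (alfa = 5%, beta = 20"%).
- SF-36: "general health (GH) is estimated to be 60 (SD = 22"), with an expected effect of 10 points, leading to "A total number of 154 patients are needed in the trial (alfa = 5%, beta = 20"%).

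The larger number is raised to 196 for a 20% dropout rate. The Statistical methods section names the two-sample t-test for the primary comparisons and gives one threshold for all tests: "The level of significance is set at p < 0.05". The only statement on multiplicity is in the Discussion: "The trial is designed with multiple statistical comparisons so results will be interpreted with caution".

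**The concern.** With two primary outcomes, the reader must know what counts as a positive trial: one particular outcome, either, or both. The article does not say. What it does state (two equal-ranking primaries, a full 5% for each in the sample size, one undivided threshold) leaves open that a significant result on either will be reported as a positive trial. Read that way, the 5% holds for each test but not for the trial's main conclusion. Caution in interpretation is a statement about tone. It does not limit how often at least one of the two tests comes out significant by chance.

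The power figures raise a related matter. Each outcome has its own 80%. If the trial's claim is later framed as a benefit on both, that figure does not describe the chance of achieving it.

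**Working it through.** **Inputs from the article.** Exercise capacity: difference 0.15, SD 0.3, so a standardised effect of 0.15/0.3 = 0.5. SF-36 General Health (GH): difference 10, SD 22, so 10/22 = 0.4545. Allocation is 1:1, alpha 5%, beta 20%, 196 randomised, 20% dropout. Sidedness is not stated; two-sided reproduces the article's numbers.

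**Input assumed.** The correlation between the two test statistics is not given. I use 0 to 0.5 as the main range and 0.8 as an extreme.

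**Step 1: reproduce the sample sizes.** Power of the two-sample t-test comes from the noncentral t with 2n − 2 degrees of freedom and noncentrality d × √(n/2).

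- Exercise: 64 per arm is the first n to reach 80% (noncentrality 0.5 × √32 = 2.83; power 80.2%). Total 128, as stated.
- GH: 77 per arm is the first n to reach 80% (noncentrality 0.4545 × √38.5 = 2.82; power 80.0%). Total 154, as stated.
- Dropout: 154/0.8 = 192.5, so 193 against the stated 196, which is close.

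Each sample size therefore uses the whole two-sided 5% for its own outcome and makes no allowance for a second primary test.

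**Step 2: error rate if either outcome suffices.** For independent tests it is 1 − (1 − 0.05)² = 1 − 0.9025 = 0.0975. For correlated tests it is one minus the bivariate normal probability that both statistics lie within ±1.96.

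| Correlation | Chance of at least one false positive |
|---|---|
| 0 | 9.75% |
| 0.3 | 9.5% |
| 0.5 | 9.1% |
| 0.8 | 7.8% |

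**Step 3: power for both outcomes.** At the planned dropout, 196 × 0.8 = 156.8, or 78 per arm; the calculated minimum is 77 per arm. Joint power is the bivariate normal probability with the two separate powers as margins.

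| Per arm | GH | Exercise | Both, corr. 0 | Both, corr. 0.3 | Both, corr. 0.5 | Both, corr. 0.8 |
|---|---|---|---|---|---|---|
| 77 | 80.0% | 86.9% | 69.6% | 71.6% | 73.3% | 76.7% |
| 78 | 80.5% | 87.4% | 70.4% | 72.3% | 74.0% | 77.3% |
| 98 (no loss) | 88.6% | 93.6% | 83.0% | 83.9% | 84.8% | 86.7% |

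The shortfall is smaller than 0.8 × 0.8 = 0.64 would suggest, because exercise capacity has more than 80% power at the sample size that GH requires.

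**Step 4: power if alpha is split.** At 2.5% each and 77 per arm, power is 71.1% for GH and 79.8% for exercise capacity.

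**The case against.** Four points can be made for the plan.

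1. **The rule may exist elsewhere.** The Statistical methods section refers to a predefined statistical protocol that is not shown. It may contain a test order or a split, and testing each outcome at 5% is compatible with a fixed sequence or with a both-required rule. This stands, and it is why confirming an existing rule would be enough. It does not remove the point, because the article itself addresses multiplicity and offers only caution.

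2. **The outcomes may support two separate claims.** The hypotheses are listed as separate bullets, and the two primaries were chosen to cover different domains. One claim per outcome, each at 5%, is a natural reading, and whether it needs joint error control is debated. This stands as far as it goes. The 9 to 10% applies only where a win on either is taken as success for the programme. If separate claims are intended, the article should say so.

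3. **The 80% was never offered as joint power.** A reader might infer that the stated power is wrong because the conclusion mentions quality of life and physical function together. The documents do not support that. The Sample size section gives 80% for each outcome, both figures reproduce, and the both-needed reading rests on one conjunction in a closing paragraph.

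4. **Any joint shortfall depends on dropout.** It appears at the planned 20% loss. With all 196 analysed, joint power would be about 83 to 85% at correlations of 0 to 0.5. This is correct.

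**Conclusion.** The point holds in a limited form. The article fixes two unordered primaries, a full 5% for each and one undivided threshold, and it has no error-controlling rule. If success on either is accepted, the error rate across the two primaries is 9.75% when they are independent and 9.1% at an assumed correlation of 0.5. Even at 0.8 it is 7.8%.

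It would go too far to say that the trial has neither its error rate nor its power whatever rule is chosen. A pre-declared fixed sequence keeps 5% overall and about 80% for the first outcome at the present sample size. The 80% per outcome is right as a marginal figure. Only if both outcomes are required does the relevant power become about 70 to 74%, and this rests on the planned dropout and on correlations of 0 to 0.5.

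**What to change.** Before unblinding, state one rule in the statistical protocol and in the report, or confirm the rule already there. Any of these would do:

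- **(a) Fixed sequence**, in an order that the sponsor justifies, since the article ranks neither outcome. For example, SF-36 General Health first and then exercise capacity, each at two-sided 5%. The first keeps about 80% power. The second can be claimed only after the first, so the power for that claim is the joint power, about 70 to 74% at the planned dropout and correlations of 0 to 0.5.
- **(b) Bonferroni or Holm split.** Bonferroni gives about 71% for General Health and 80% for exercise capacity at 77 per arm. Holm gives at least as much.
- **(c) Both required**, each at 5%, with joint power stated as about 70 to 74% at the planned dropout and about 83 to 85% if all 196 are analysed.

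Whichever is chosen, describe the 80% as power per outcome. The cost is one paragraph and no extra patients. Enrolment is already complete, so the sample size cannot easily change, but the rule still can be declared. The downside is a less favourable power figure or a conditional second claim.

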### Sample size

#### Physical capacity

Based on current knowledge (1), we estimate a difference in V02max of 15% between the rehabilitation group and standard care group (SD = 0.3). A total number of 128 patients are estimated for the trial (alfa = 5%, beta = 20%). *Health status outcome measure: *Based on health status measures among a Danish population compared to patient with heart disease a baseline mean-score of the SF-36 general health (GH) is estimated to be 60 (SD = 22). The effect of rehabilitation is expected to be 10 absolute points. A total number of 154 patients are needed in the trial (alfa = 5%, beta = 20%). The study includes 196 patients, taking a drop-out rate of 20% into account. In the previous trials a drop-out rate around 20% was found, with no significant differences in baseline information on any study variable between groups and no difference in the number of dropouts in each group [11,17,19,21,23].

### Blinding

Because of the nature of rehabilitation, the interventions are open to the staff and the patients. A blinded investigator performs all physical tests, data collection and administration. Blinded outcome analyses are conducted.

### Statistical methods

The statistical analyses of the effects of rehabilitation are conducted based on a predefined statistical protocol using SPSS 17.0 for Windows. The analysis will adopt an analytical approach on all available data, meaning that all data obtained are included in analyses, regardless of adherence to the study protocol. Only data from patients following through the program will be included in the analysis of the endpoints. Accordingly, there is no imputation of missing data. Questionnaire responses will be converted to numerical scores using standard methodologies. Continuous data are checked for normality of distribution, and log-transformed if required. The baseline characteristics will be presented by group to present similarities across treatment, but according to recommendations no significant testing will be performed [43]. The socio-demographic and clinical characteristics of individuals who drop out from the study will be compared with those who completed the study and drop-out characteristics between groups will be compared. The effectiveness of the intervention will be examined using blinded analysis of variance. The primary comparisons will be Two independent samples T-test for the mean difference between two independent samples. Paired T-tests of equality of means will be used for within group analysis of difference over time. Further, univariable and multivariable regression analysis will also be used to investigate the effect of the intervention on the endpoints. The type of regression analysis will depend on the endpoint in question. Demographic, clinical and questionnaire data will be included in multivariable analysis in order to control for their potential confounding effects. The level of significance is set at p < 0.05. Data will, for continues data, be shown as means ± standard deviation or percentage. Categorical data will be shown as percent. Twelve month follow-up data and results obtained from Danish registries regarding hospitalisations are used for follow-up comparison. Due to the skewed distribution of length of hospital stay and repeated measurements of hospital admissions on patients these register-based tertiary outcomes will be analyzed using multivariate random-effect modelling with patients as random effects. Further analysis will be conducted using the Cox regression model including time to first event as outcome variable. At baseline 46% (n = 91) of the population was employed. This is a rather small number of patients and sickness absence will be included as a measure when evaluating employment status. The direct costs of healthcare are calculated by a retrospective top-down method [44]. All other costs are extracted from relevant registers.

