### Randomisation

Before randomisation baseline data were collected. Patients were randomised while in hospital.

The enrolling research assistant or primary investigator called for randomization allocation. Randomisation (block of 4) was done by voice-respondent in a 1:1 ratio to intervention group or control group (standard care) and there was stratification according to gender and left ventricular ejection fraction (below or above 35%).

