#### Standard care

Patients in the control group follow the standard care procedure, which is medical follow-up and an invitation to participate in a 2 hour group meeting, which includes information about the ICD and exchange of experiences among patients. In the standard care group no psycho-educational follow-up or exercise training are provided. A bias may occur if patients are offered cardiac rehabilitation at their local hospital. As a national law encourages rehabilitation for all cardiac patients, it is not possible to completely avoid participation in local initiatives. Patients are asked whether they had participated in such activities at the12 months follow-up.

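### Two adjacent sentences set incompatible analysis sets, and the one naming the endpoints, read literally, selects patients after randomisation on completing a programme only one arm receives

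*Protocol article*

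**What the plan says.** Three consecutive sentences in the Statistical methods section of the protocol article define who is analysed.

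- The first describes an all-available-data approach, in which "all data obtained are included in analyses, regardless of adherence to the study protocol".
- The second says: "Only data from patients following through the program will be included in the analysis of the endpoints".
- The third draws the missing-data rule from this: "Accordingly, there is no imputation of missing data".

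Neither inclusion rule is tied to a particular endpoint or to a primary, secondary or sensitivity analysis.

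Three other places bear on the meaning.

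- Standard care: "In the standard care group no psycho-educational follow-up or exercise training are provided".
- Sample size: "The study includes 196 patients, taking a drop-out rate of 20% into account".
- Discussion: "There is an expected drop-out rate at 20% which could influence the validity", followed by "Any difference between patients completing the intervention and those not completing (drop-outs) will be carefully discussed". Here a drop-out is someone who did not complete the intervention.

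**The concern.** Take an intervention patient who stops training but returns the 6-month SF-36. The first rule includes this patient and the second excludes the same patient. The plan therefore does not determine the analysed population for either primary outcome. If the choice is left until results are visible, it becomes an uncontrolled analyst decision.

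The second rule is the more troubling because it is the one that names the endpoints. Completing a year of nurse consultations and twelve weeks of training happens after randomisation and may depend on health and motivation. Controls have no such programme to complete. Under a literal application, the completers in one arm would be compared with a control group not selected in the same way. Randomisation no longer guarantees that such groups are comparable.

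The rule would also remove outcomes that are available. The article says that the national registries lose only a small percentage of data, so death and hospitalisation would be known for non-completers. An intervention patient who died during the programme year would not have followed it through, and the literal rule would drop that death from the mortality comparison.

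**Working it through.** **The plan's own figures.** The article gives, for SF-36 general health (GH), SD 22, a difference of 10, alpha 5% and power 80%. Two-sided testing is assumed, since sidedness is not stated.

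- GH: n per arm = 2 × (1.960 + 0.842)² × 22² / 10² ≈ 76, or 77 with the exact t-test, so 152 to 154 in total. The plan states 154.
- VO2max, difference 0.15 and SD 0.3: n per arm = 2 × (1.960 + 0.842)² × 0.3² / 0.15² ≈ 63, or 64 exactly, so 126 to 128. The plan states 128.
- Drop-out: 154 / 0.80 = 192.5, so 193. The plan states 196.

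The sample size reproduces. With 20% lost, 196 × 0.80 ≈ 157 patients remain and power for 10 points is about 81%. The allowance therefore covers lost numbers. It does nothing about which patients are lost.

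**Side-by-side reading.**

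| Patient | All-data sentence | Following-through sentence |
|---|---|---|
| Intervention, completed, outcome known | in | in |
| Intervention, stopped, outcome known | in | out |
| Control, outcome known | in | not defined: no programme to complete |

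The second row is the contradiction. The third is the asymmetry.

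**Bias formula.** Let d be the share of an arm that is excluded, and δ the mean outcome of completers minus that of non-completers in that arm. Excluding non-completers raises the arm mean by d × δ. The bias in the between-arm difference is therefore

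bias = d(I) × δ(I) − d(C) × δ(C),

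with I for intervention and C for control.

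**Illustration.** The assumptions, none of which the documents supply, are d(I) = 0.20, d(C) = 0 and no true effect. The 196 patients are taken as 98 per arm, and SD 22 comes from the sample size section. About 78 intervention patients and 98 controls are then analysed.

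SE = 22 × √(1/78 + 1/98) = 3.34

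Type I error = P(|Z + bias/SE| > 1.96)

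| δ(I), GH points | Bias = 0.20 × δ(I) | Share of planned 10 points | bias/SE | Type I error |
|---|---|---|---|---|
| 5 | +1.0 | 10% | 0.30 | 6.0% |
| 10 | +2.0 | 20% | 0.60 | 9.2% |
| 15 | +3.0 | 30% | 0.90 | 14.6% |

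**Other cases of the same formula.**

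- Equal shares and equal gaps in both arms, for example d = 0.20 and δ = 10 in each: 2.0 − 2.0 = 0.
- Non-completers better by 10 points, no controls excluded: 0.20 × (−10) = −2.0, against the programme.

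No matching figure is given for the exercise test, because the documents offer no basis for a completer gap on that outcome.

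**The case against.** The strongest defence is that the three sentences describe one ordinary available-case analysis: use whatever was obtained, analyse those who stayed in follow-up, and impute nothing. Several points in the article favour this.

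- The Statistical methods section later contrasts people who left the study with people who completed it, which concerns the study and not the intervention.
- The same section plans to compare drop-out characteristics between groups, which presupposes drop-outs in both arms.
- All patients had to agree to the entire programme before randomisation, so the word could cover trial participation in either arm.
- The 20% allowance applies to all 196 patients, and the earlier trials cited had similar drop-out numbers in each group.

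This stands as a possible reading, but the text does not state it. The sentence refers to the programme, controls receive none, and the Discussion equates drop-outs with patients not completing the intervention. A reader has to guess.

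The defence does rule out some stronger inferences. A reader might conclude that exclusions will certainly fall on the intervention arm alone, that bias will favour the programme, and that both primary outcomes will be inflated. The documents support none of these as fact. They give no outcome difference between completers and non-completers. Patients who stop may be sicker, or may be well and back at work.

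The article's mitigations do not settle the matter either. Comparing drop-outs with completers describes selection without removing it. The multivariable regressions can adjust only for measured characteristics. Balanced drop-out in earlier trials does not show that non-completers here have the same outcomes as completers.

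A separate statistical protocol exists and is not shown. The point does not depend on its content, because the published text itself states two incompatible rules.

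**Conclusion.** The point holds as a contradiction in the stated analysis set. Read literally, the second rule forfeits the protection of randomisation for every endpoint and discards outcomes that are known. This follows from the article's text alone.

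The size is conditional. Under the one-sided scenario above, the bias is 1 to 3 GH points against a planned effect of 10, with a type I error of about 6% to 15%. If controls were lost at the same rate and with the same gap, the bias would be near zero. If non-completers did better, its sign would reverse. The figures show what the wording permits; they are not a forecast. The rule should be settled before the endpoints are analysed.

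**What to change.** Delete the sentence restricting the endpoint analysis to patients who follow the programme through. State instead that the primary analysis of every endpoint includes all randomised patients in their allocated arm, with all outcome data obtained, whatever their adherence to or withdrawal from the programme. If a completers analysis is wanted, keep it as a labelled secondary per-protocol analysis and define what completion means in each arm.

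A likelihood-based repeated-measures model for the SF-36 and a sensitivity analysis for missing outcomes would be reasonable additions. They are optional and not needed to resolve the contradiction.

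The cost is a change of wording and little extra analysis. Enrolment closed in November 2009. If outcomes were not collected from patients who stopped, some may be unrecoverable and would remain missing. The estimated effect may be slightly smaller than among completers. If the planned 10 points refers to completers, and 20% of the intervention arm gained nothing, the effect would be 0.80 × 10 = 8 points. Power with all 196 patients would then be about 72%, against 89% for 10 points.

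### With 20% drop-out expected, the primary SF-36 comparison is a t-test without imputation that ignores drop-outs' earlier scores and is biased if health-related drop-out differs between arms

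*Protocol article*

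**What the plan says.** In the protocol article, Statistical methods, four statements bear on this point:

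- All data obtained are to be analysed regardless of adherence.
- The next sentence limits the endpoint analysis to patients who follow the programme through.
- From that it concludes: "Accordingly, there is no imputation of missing data".
- The primary comparison is a t-test for two independent samples. Univariable and multivariable regressions come in addition.

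Sample size expects loss: "The study includes 196 patients, taking a drop-out rate of 20% into account". Discussion concedes the risk: "There is an expected drop-out rate at 20% which could influence the validity". The stated response is to compare drop-outs with completers, compare drop-out characteristics between groups, and discuss the differences.

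Outcomes (Table 2) schedules SF-36 at baseline, 3, 6 and 12 months. The exercise test, the other primary outcome, is done at 3 and 6 months only. Randomisation states that baseline data were collected before allocation. No section names the primary time point for SF-36; 12 months is assumed below.

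**The concern.** A t-test uses only patients who have the endpoint value. With no imputation, a patient missing that value drops out of the comparison along with up to three earlier SF-36 scores that show how the patient was doing. Deleting the completers-only sentence would not cure this, because the final value would still be absent.

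What is at stake is bias. If the link between poor health and leaving is stronger in one arm than in the other, the patients left in the two arms are no longer comparable and the estimated effect shifts. Raising the sample size does not help, and describing the drop-outs leaves the estimate where it was.

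There is reason to doubt that the link is equal. The intervention arm has nine nurse consultations over a year and twice-weekly training for twelve weeks. Controls have medical follow-up and an invitation to one group meeting. Under Blinding, the interventions are open to patients and staff.

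**Working it through.** **1. The plan's own figures.** Inputs from Sample size: "The effect of rehabilitation is expected to be 10 absolute points"; "general health (GH) is estimated to be 60 (SD = 22"); alpha 5% (two-sided assumed), power 80%.

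- Normal formula: n per arm = 2 × (1.960 + 0.842)² × 22² / 10² = 76, total 152. The t-based version gives 76.95, so 77 per arm and 154 in total, as stated.
- Inflation: 154 / 0.8 = 192.5, so 193; the plan has 196.
- After 20% loss: 196 × 0.8 = 157 patients, power about 0.81 for 10 points.

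The sample size is sound. The inflation protects power and does nothing about bias.

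**2. Size of the bias in general.** If a share d of an arm drops out, the completers' mean exceeds the whole arm's mean by d × (completer mean − drop-out mean). The bias in the arm difference is this product for intervention minus the same product for control. With d = 0.20 and an assumed gap of 5 to 15 points in the intervention arm only, the bias is 0.20 × 5 = 1 to 0.20 × 15 = 3 points. With equal shares and equal gaps it is zero.

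**3. Simulated trials, no true effect.** From the article: SD 22, 20% missing, 196 patients. Arms of 97 control and 99 intervention are inferred from Table 3 (76 is 78% of 97; 79 is 80% of 99). Assumed: visit correlations 0.5 to 0.7, endpoint at 12 months, drop-out depending on the 6-month score. The odds of drop-out per SD lower score are exp(0.7) = 2.0, exp(1.2) = 3.3 or exp(0.4) = 1.5.

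| Drop-out depends on a low score in | Complete-case bias (points) | Type I error |
|---|---|---|
| neither arm | 0.0 | 5.1% |
| intervention only, odds × 2.0 | +1.9 to +2.0 | 8.9 to 9.1% |
| intervention only, odds × 3.3 | +3.0 to +3.1 | 12.9 to 13.2% |
| both arms, odds × 2.0 | 0.0 | 5.6% |
| intervention × 2.0, control × 1.5 | +0.8 | 6.0% |
| control only | −2.0 | mirror image of intervention only |

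The ranges come from 1,500 and 4,000 trials per scenario. On the first three mechanisms a likelihood repeated-measures model had bias within 0.1 point and type I error of 3.9 to 5.2%.

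Hand check of the error rates: the complete-case SE is 22 × √(1/77.6 + 1/79.2) = 3.51. A bias of 2 is 0.57 SE, giving Φ(−1.39) + Φ(−2.53) = 8.8%. A bias of 3 is 0.855 SE, giving Φ(−1.105) + Φ(−2.815) = 13.7%. Both agree with the table.

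**4. Large-sample check, true effect 10 points.** 20% drop-out in each arm, odds × exp(1) = 2.7 per SD, score taken relative to the arm's own mean, correlation 0.5 to 0.7:

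- Low 3-month score, intervention only: complete-case 11.9 to 12.7. Baseline-adjusted complete cases 10.9 to 11.0. A missing-at-random method using baseline and 3-month scores 10.0.
- Same dependence in both arms: about 10 by every method.
- Unseen final score, intervention only: complete-case 13.7 to 13.8; missing-at-random method 11.7 to 12.6, so only partly corrected.

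**5. Precision.** With nobody missing, the unadjusted SE is 22 × √(1/97 + 1/99) = 3.14. The repeated-measures model reached about 2.9 with a common baseline mean and about 3.3 with free baseline means. Complete-case analysis adjusted for baseline gave 3.05.

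**The case against.** The strongest reply is that the harm depends on a mechanism the article does not give. A reader might infer that the t-test is valid only if drop-out is unrelated to health, or that it must favour the programme. Neither holds. Equal dependence in both arms leaves the difference unbiased, and dependence in controls alone turns the bias against the programme. A reader might also suppose that controls merely return questionnaires. Table 2 does not support that: exercise tests and device interrogations are trial outcomes, and a between-arm exercise comparison needs controls to attend.

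Sample size adds that earlier trials found similar baseline data and equal numbers of drop-outs between groups. That is relevant, but equal numbers do not show equal reasons, and baseline data say nothing about health after baseline.

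The planned multivariable regression could adjust for baseline SF-36. It is additional, not primary, and as worded it adds no final values for drop-outs. In step 4 baseline adjustment left about 1 point of bias when drop-out followed the 3-month score.

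It is also fair that a predefined statistical protocol is cited and not shown, so the absence of a sensitivity analysis here is not in itself a fault. The t-test and the no-imputation rule, however, are stated outright.

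Finally, the smaller SE of the repeated-measures model might be read as information recovered from drop-outs. Since 2.9 lies below the full-data 3.14, the gain comes mainly from baseline adjustment and should not be claimed for missing-data recovery.

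**Conclusion.** The point holds in a limited form. As written, the primary SF-36 analysis discards patients without the final value together with their earlier scores, and nothing in the plan corrects the estimate if health-related drop-out differs by arm.

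Under drop-out tied to the 6-month score in the intervention arm only, the bias is about +2 to +3 points, or 20 to 30% of the planned 10-point effect, with type I error of 9 to 13%. These are illustrations. The visit correlations, the drop-out mechanism and the 12-month endpoint are assumptions, and the true bias could be near zero or negative. The article establishes neither its size nor its direction; it does establish that the chosen method is exposed to it.

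The change is advisable because it uses data already scheduled, but the planned analysis is not shown to be wrong in every case.

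**What to change.** In Statistical methods, replace three sentences together: the t-test sentence (for SF-36), the completers-only sentence and the no-imputation sentence. Changing the last alone would leave the other two contradicting the new analysis, and a likelihood mixed model involves no imputation anyway. Suggested text:

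*SF-36 is analysed in all randomised patients, whether or not they follow through the programme, by a likelihood-based mixed model for repeated measures using all available baseline, 3-, 6- and 12-month values (visit, arm-by-visit with a common baseline mean or baseline adjustment, gender, LVEF stratum, unstructured covariance). The contrast is the arm difference at the primary time point.*

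Name that time point. Report deaths separately rather than as ordinary missing values. Add a delta-adjusted sensitivity analysis, because the model removes bias only if values are missing at random.

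The cost is wording, modest programming and an assumption that must be stated; no extra patients or visits are needed. The remedy covers SF-36. The exercise test has only a 3-month earlier value, so correction there is more limited.
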